Furthermore, an increased susceptibility to certain adverse drug reactions may partly be due to genetic polymorphisms that alter responses of individual persons to various drugs [13]. A possible cause might be the pathway of hepatic drug metabolization by the cytochrome P-450 family of biotransformation enzymes [20]. Consequently, poor, extensive and ultra-rapid metabolizers for certain cytochrome pathways and membrane bound transporters can be distinguished [21], which influence the pharmacodynamics and pharmacokinetics. The majority of fall-risk increasing drugs are metabolized by a small number of enzymes, the major ones being CYP450 2D6, 2C9, 2C19 and 3A4/5 [22]. Due to polypharmacy among older adults, the risk of a CYP 450 interaction increases.

A systematic fall-related drugs assessment combined with medication changes and a one-year follow-up assessment among older fallers may contribute to a reduction in the incidence of new falls and related consequences [19]. At this moment a structured medication assessments are not part of standard care of older fallers presenting at the Emergency Department. In the Netherlands, the current care of fall-related injuries consists of treatment of the injuries of the fall. However, before a systemic fall-related medication assessment can be incorporated in the routine work-up of older persons presenting with a fall, further evidence is required. The aim of this randomized controlled trial is to compare the effect of withdrawal of fall-risk increasing drugs versus 'care as usual' on future falls. The primary outcome of this study is be the number of new falls and fallers. Secondary outcome measurements are possible health effects of medication withdrawal, health-related quality of life, costs, and cost-effectiveness of the intervention.

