### Outcome measures

The primary outcome measure will be the incidence of new falls, fallers, based on the Falls Calendar. Secondary outcome measures will be fall-related injuries, generic health-related HRQoL, compliance, quality adjusted life years (QALY), genetic polymorphisms associated with increased adverse drug reactions, and positive or negative health effects, cost, and cost-effectiveness.

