### Follow-up

Patients will be followed for one year. After the first visit to the research outpatient clinic patients receive a Falls Calendar [33]. During a one-year follow-up period, the participant will be asked to record every week whether they have experienced a fall that week. The 3-monthly calendar sheet will be returned once per 3-months by mail. Cost-effectiveness will be measured using a cost-evaluation questionnaire. Participant can register the number of visits to physicians, therapists, day care centers, hospitalizations, adaptations of the living area, and the current living location (*e.g*., home or nursing home). The cost-evaluation questionnaire will be returned with the falls calendar at three, six, nine, and twelve months after the first visit to the research outpatient clinic. In case no calendar sheet or questionnaire is received, or when it is completed incorrectly, the calendar sheet or questionnaire will be completed by telephone.

During the last visit to the outpatient clinic, one year after the first visit, all physical performance tests are conducted, as well as questionnaires regarding medical history, drug use, quality of life, and fall risk profile. Adherence to the drug-use recommendations (complete withdrawal, lowering of dosage, or substitution) will be evaluated by reassessment of drug use as described above. Information of the participants regarding medical history and drug use will be verified by the General Practitioner and local pharmacist.

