### Sample size calculation

A total number of 620 patients will be included in the study, 310 in the control group and 310 in the intervention group. Calculation of the required sample size is based on the assumption that the annual cumulative incidence of further falling is 50% without intervention [40], a 15% drop-out (including death) [11], drug withdrawal being possible in 50% of the participants in the intervention group and a 50% decrease of further falls among participants with successful withdrawal [18]. A single-sided test with an alpha level of 0.05 and a beta of 0.2 indicates that 310 patients in both groups is sufficient in order to detect a 25% decrease of respondents reporting further falls in the intervention group.

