### Statistical analysis

Data will be primarily analyzed according to the intention-to-treat principle. Patients with protocol violations will be followed up, and data will be recorded. Data will be analyzed with and without inclusion of patients with protocol violation. At baseline, differences in baseline characteristics will be compared between the intervention and control group in order to assess comparability between the two groups. Student's T-test (parametric numeric data), Mann-Whitney U-test (nonparametric numeric data) or Chi-square test (categorical data). Data will be presented as mean ± SD (parametric data) or medians and percentiles (non-parametric data).

The hazard ratio for falling will be calculated using a Cox-regression model. Herein, the time between the intervention (*i.e*., drug assessment/change or not) and the first and/or second fall will serve as the primary outcome measure. Fallers will be defined as those who will fall once or more during the one-year follow-up. Differences in cumulative incidence of falls will be analyzed using log-linear or Poisson regression, adjusted for over dispersion because of interdependence among the dependent variable (falls). Differences in adverse health effects between both trial arms will be assessed using Chi^2 ^testing. Several subgroups will be distinguished in order to examine whether the effect of the intervention depends upon sex, age, race and risk of future falls. Since healthcare costs per patient are typically highly skewed, non-parametric techniques will be used to derive a 95% confidence interval for the differences in distributions of the costs. In a sensitivity analysis the impact on cost-effectiveness of statistical uncertainty on the main study outcomes will be determined (uni- and multi-variable).

The association between genetic polymorphisms and falls history will be evaluated using a multivariate logistic regression analysis. A *p*-value of < 0.05 will be used as threshold for statistical significance.

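### The protocol calls falls, fallers and time to the first and/or second fall primary without naming one deciding test, which could roughly double the false-positive rate

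*Protocol article*

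**What the plan says.** Four sections of the protocol article bear on the primary outcome.

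- Background: "The primary outcome of this study is be the number of new falls and fallers". This is a count and a proportion.
- Outcome measures: "The primary outcome measure will be the incidence of new falls, fallers, based on the Falls Calendar". These are the same two constructs, again side by side and unranked.
- Statistical analysis: a Cox model for the time from the intervention, "and the first and/or second fall will serve as the primary outcome measure". Then come a definition, "Fallers will be defined as those who will fall once or more during the one-year follow-up", and a second analysis: "Differences in cumulative incidence of falls will be analyzed using log-linear or Poisson regression, adjusted for over dispersion". The section ends with a single significance threshold of p < 0.05 that is not tied to any one outcome and gives no sidedness.
- Sample size calculation: 310 per arm, single-sided alpha 0.05 and beta 0.2, "in order to detect a 25% decrease of respondents reporting further falls in the intervention group". This is the proportion of fallers and nothing else.

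**The concern.** A count of falls, a proportion of fallers and a time to event are different quantities, and each is labelled primary somewhere in the current text. The words and/or add a further ambiguity, because time to first fall, time to second fall and the two together are different analyses. With no ranking and no alpha split, a trial that is significant on fall rate but not on fallers, or the reverse, could be described as positive or negative on its primary outcome with equal support from the protocol.

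The error rate attached to a claim of primary success would then exceed the nominal 5%. The routes that add most to it, fall count and second fall, are the ones for which no power was calculated. The Randomization section says that neither patients nor geriatrician can be blinded, and falls are self-reported, so a deciding test fixed in advance is an important safeguard.

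**Working it through.** **1. What the sample size covers.** Inputs from Sample size calculation: control proportion 0.50; effect 50% withdrawal × 50% decrease = 25%, so the intervention proportion is 0.50 × 0.75 = 0.375; power 80%; drop-out 15%.

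Formula per arm: n = [z_α √(2p̄(1−p̄)) + z_β √(p₁(1−p₁) + p₂(1−p₂))]² / (p₁−p₂)², with p̄ = 0.4375.

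- Two-sided 0.05: (1.960 × 0.7016 + 0.842 × 0.6960)² / 0.125² = 3.846 / 0.015625 = 246.1, so 247. With continuity correction, (n/4)[1 + √(1 + 4/(n × 0.125))]² gives 262. Then 262 / 0.85 = 308.2, so 309.
- Single-sided 0.05, as stated: 194, then 194 / 0.85 gives 229 (248 with continuity correction).

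The planned 310 is thus reproduced, within rounding, as a comparison of fallers tested two-sided with continuity correction. The mismatch with the stated single-sided test is a separate point. Here it shows that the sidedness also needs fixing and that no other endpoint entered the calculation.

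**2. How much the open choice could cost.** Null simulation with the same fall process in both arms:

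- Evaluable per arm: 310 × 0.85 = 263.5, taken as 263.
- One year of follow-up; 50% of each arm falls at least once.
- Falls follow a gamma-Poisson model with shape k. Setting (1 + m/k)^(−k) = 0.5 gives a mean m = k(2^(1/k) − 1): 1.5 falls for k = 0.5, 1.0 for k = 1 and 0.83 for k = 2. The shapes are an assumption, since the protocol gives no dispersion.
- Tests, each at 0.05: log-rank on time to first fall (standing in for Cox), log-rank on time to second fall, and quasi-Poisson on fall rate.

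Chance of at least one significant result under no effect, across the three shapes and repeated runs:

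| Tests counted | Two-sided, either direction | Single-sided, favouring the intervention |
|---|---|---|
| First fall, second fall, fall rate | about 9% to 11.5% | about 9.5% to 10.3% |
| First fall, fall rate | about 7% to 9% | – |

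Each test alone stays close to 5%.

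**3. Why it is not larger.** If the tests were independent, three would give 1 − 0.95³ = 14.3% and four would give 1 − 0.95⁴ = 18.5%. They are correlated: about 0.98 between proportion of fallers and time to first fall, and about 0.5 to 0.84 for the other pairs. Fallers and first fall are therefore almost one test, and the extra routes come mainly from the fall count and the second fall.

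**4. What the repair does to power.** With fallers as sole primary outcome, 263 evaluable per arm gives 82.6% power two-sided or 89.5% single-sided, without continuity correction. Three co-primary outcomes at 0.05/3 would need 388 per arm two-sided or 326 single-sided. At 263 evaluable, power on fallers would fall to 69.1% or 77.9%.

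**The case against.** The best defence is that the sections can be read together. Background and Outcome measures agree on two constructs, and Statistical analysis could simply be giving the method for each: Cox for falling, with faller defined in the next sentence, and Poisson or log-linear regression for the number of falls. An analysis plan that is not shown may contain a hierarchy. Part of this stands: fallers and first fall are nearly one test, so the conflict is smaller than a count of labels suggests. It does not remove the fall count as a second primary quantity, the second fall as a third, or the missing ranking. An unseen plan could settle the choice, but the conflicting labels are in this text.

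Some stronger readings are tempting but not supported:

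- A reader might infer that first or second fall will be picked once the data are known. The protocol does not say so; and/or may equally mean that both are analysed.
- A reader might count fallers as a fourth test and quote a higher error rate. Statistical analysis names no separate between-arm test for that proportion.
- A reader might take the two-sided 9% to 11.5% as the chance of a false claim of benefit. It includes false findings of harm. With two-sided tests, false findings in favour of the intervention come to about 5.0% to 5.5%, against a nominal 2.5%.
- Follow-up says that "the participant will be asked to record every week whether they have experienced a fall that week", and a reader might infer that falls cannot be counted. This is a one-sentence summary of a cited calendar that is not shown, and Outcome measures bases the incidence of falls on it. The text does not establish that counts are missing.

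**Conclusion.** The concern holds as a contradiction in the current text: different quantities carry the label primary, only the proportion of fallers is sized, and no deciding test is named. If any of first fall, second fall or fall rate could count as primary success, the false-positive rate is roughly double the nominal level: about 9% to 11.5% against 5% two-sided in either direction, or about 10% against 5% single-sided in favour of the intervention. Without the second fall it is about 7% to 9% two-sided.

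The figures rest on the protocol's own 50% fallers, 15% drop-out and 310 per arm, and on assumed gamma-Poisson falls with shape 0.5 to 2. They describe what the wording would allow, and are not evidence that the investigators intend to choose among results.

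**What to change.** Before the outcome data are analysed, name one primary outcome, one deciding test and its sidedness, and use them identically in Background, Outcome measures, Sample size calculation and Statistical analysis. The choice that fits the sample size is being a faller within one year. It can be analysed as the proportion of fallers, which is the quantity sized, or as time to first fall by Cox regression, which is nearly equivalent. The sponsor should pick one of the two.

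Remove the second fall from the primary definition. List time to second fall and fall rate (adjusted for overdispersion, with follow-up time as offset) as secondary outcomes in a stated order. If the sponsor prefers to keep more than one primary outcome, state the hierarchy or alpha split and restate the power.

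The cost of the single-outcome route is an amendment to the wording, with no extra patients. The downside is that a positive fall rate or second-fall result alone could no longer be claimed as primary success. Keeping three outcomes with an equal split costs either sample size or power, as shown in the working.

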The QALY combines mortality and morbidity into a single number. The morbidity component is referred to as HRQoL and is based on a descriptive health-state measure. Because of a long track record in health economic analyses, the EQ-5D measure will be used for this purpose [28]. Furthermore, the lifetime health effects (cardiovascular events such as myocardial infarction, stroke, and mortality) due to possible increased cardiovascular risks (*i.e*., cardiac failure, rebound hypertension) will be calculated with existing models for cardiovascular disease risk management. In accordance with guidelines for differential discounting, effects will be discounted at a rate of 1.5% and costs at 4% per year [39].

Full blood for DNA isolation will be drawn during the first visit (5 mL). The blood will be stored at -80 degrees Celsius, until DNA-isolation will take place. After DNA isolation, polymorphisms (CYP1A2, CYP2C9, CYP2C19, CYP2D6, CYP2E1 en CYP3A4) will be analyzed using the TaqMan allelic discrimination assays on the ABI Prism 9700 HT sequence detection system. If needed, other polymorphisms will be added to the analysis.

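### Adverse health effects are compared by a chi-square test at p < 0.05; for uncommon harms a non-significant result would be uninformative, so report a risk difference with a confidence interval

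*Protocol article*

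**What the plan says.** The Outcome measures section lists positive or negative health effects among the secondary outcomes. The Statistical analysis section gives one between-arm method for them: "Differences in adverse health effects between both trial arms will be assessed using Chi^2 ^testing". It closes with a general criterion, a p-"value of < 0.05 will be used as threshold for statistical significance".

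The same section fixes a hazard ratio for falling and a 95% confidence interval for the cost difference. It names no effect measure or interval for harm.

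Table 2 includes antihypertensives, anti-arrhythmics, nitrates and digoxin among the drugs to be stopped, reduced or substituted. The Costs section plans to model lifetime cardiovascular effects "due to possible increased cardiovascular risks", giving cardiac failure and rebound hypertension as examples.

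The sample size rests on fallers alone. It assumes that "the annual cumulative incidence of further falling is 50% without intervention" and concludes that "310 patients in both groups is sufficient in order to detect a 25% decrease of respondents reporting further falls". It also assumes 15% drop-out, deaths included, and that withdrawal is possible in half of the intervention arm. The article gives no expected rate for any adverse event.

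**The concern.** A chi-square test returns a p-value, with neither the size nor the direction of a difference. That is a limited summary for the harm side of a drug-withdrawal trial, and more so when the sample size comes from a common outcome. If serious events are uncommon, a non-significant result is likely whether or not withdrawal does harm, and the p-value cannot separate these two cases.

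The Discussion offers the results to clinicians and policymakers deciding whether withdrawal belongs in falls prevention. They will need to know how large an excess of harm the data can exclude, and the named analysis does not tell them.

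**Working it through.** **Inputs.** From the Sample size calculation section: 310 per arm, 15% drop-out, so 310 × 0.85 = 263.5, taken as 263 completers; withdrawal possible in 50% of the intervention arm. From the Statistical analysis section: chi-square test, threshold 0.05. A 2×2 chi-square is non-directional, so two-sided 0.05 (z = 1.96) is used. Control-arm event risks are **assumptions**, shown as a range.

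**The plan's own figure.** For fallers at 50% vs 37.5% with 80% power, the usual two-proportion formula gives:
- one-sided 0.05, as stated: 194 per arm, 229 after 15% drop-out
- two-sided 0.05 with continuity correction: 262 per arm, 262 / 0.85 = 308.2, so 309

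The planned 310 therefore matches the two-sided corrected calculation and not the stated single-sided test. That is a separate matter to reconcile; the power for harm below simply takes 310 as planned.

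**Power of the chi-square test for harm.** With risks p1 and p2, mean p̄ and n per arm:

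power = Φ{ [ |p2 − p1|·√n − 1.96·√(2p̄(1 − p̄)) ] / √(p1(1 − p1) + p2(1 − p2)) }

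Example, 3% vs 6%, n = 310: (0.03 × 17.607 − 1.96 × 0.2932) / 0.2924 = (0.5282 − 0.5746) / 0.2924 = −0.159, and Φ(−0.159) = 0.437.

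Doubling across the whole arm:

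| Assumed control risk | Intervention risk | Power, n = 310 | Power, n = 263 |
|---|---|---|---|
| 1% | 2% | 17% | 15% |
| 2% | 4% | 31% | 27% |
| 3% | 6% | 44% | 38% |
| 5% | 10% | 66% | 59% |
| 7% | 14% | 81% | 75% |
| 8% | 16% | 87% | 81% |
| 10% | 20% | 94% | 90% |

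Solving the formula for the control risk gives 50% power at 3.5% (n = 310) or 4.1% (n = 263), and 80% power at 6.8% or about 7.9%. Exact enumeration of the Pearson test at n = 310 gives 16%, 31%, 44% and 67% at control risks of 1%, 2%, 3% and 5%, so the approximation is adequate. Read one-sided at 0.05, the 50% point falls to about 2.5 to 2.9%.

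**Dilution under the plan's own assumption.** If risk doubles only in the 50% who can be withdrawn, the arm-level ratio under intention to treat is 0.5 × 2 + 0.5 × 1 = 1.5.

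| Assumed control risk | Intervention risk | Power, n = 310 | Power, n = 263 |
|---|---|---|---|
| 3% | 4.5% | 16% | 15% |
| 5% | 7.5% | 25% | 22% |
| 10% | 15% | 47% | 41% |

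Power stays below 50% up to a control risk of about 10.7% (n = 310) or 12.3% (n = 263).

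**What an interval would show.** With 3% observed in both arms, the approximate half-width is 1.96·√(2 × 0.03 × 0.97 / n): 0.027 for n = 310 and 0.029 for n = 263. A result of exactly no difference would still be compatible with an excess of 2.7 to 2.9 percentage points, close to a doubling. The p-value alone conceals this.

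**The case against.** **Detail left to a fuller document.** Chi-square is a valid test for categorical outcomes, and an article may leave effect measures and intervals to the full protocol or SAP. This has weight, and missing detail alone would be no finding. But the article does make a choice here: an estimate for falls, an interval for costs and a test for harm. That choice can be improved. The contrast with costs should not be pressed, since the section ties that interval to skewed cost data.

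**Three stronger readings that the article does not support.**
- A reader might infer that p > 0.05 will be reported as safety or as no difference. The article never says so, and the Discussion makes no safety claim.
- A reader might infer that harm is judged by this test alone. It is the only between-arm analysis named, but a research nurse makes weekly calls for a month to check for negative effects, Table 1 records complications at 3, 6, 9 and 12 months, QALYs include mortality and morbidity, and lifetime cardiovascular effects are modelled. As described, none of these gives a between-arm estimate of observed harm.
- A reader might infer that any doubling would usually be missed. At a 5% control risk, a whole-arm doubling is more likely than not to be detected (59 to 66%), and at 8% power is at least 81%. The statement depends on event rates that the article does not give.

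**Denominator.** Using 263 per arm removes deaths, because drop-out includes death. This is correct, so both sizes are shown and the fix uses all randomised patients.

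**The remedy adds no power.** True. An interval from the same data will usually include zero when the test is non-significant, and without a margin it supplies no decision rule. It does show how large an excess remains compatible with the data. Low power for a secondary safety outcome is common and is not in itself the defect.

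**Conclusion.** The point holds in limited form. The only between-arm analysis named for adverse health effects is a significance test that would be uninformative, when non-significant, for uncommon harms. For a whole-arm doubling, uncommon means a one-year control risk below about 3.5% (310 per arm) or 4.1% (263 per arm). If the doubling is confined to the half assumed to be withdrawn, the range extends to about 11 to 12%.

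These limits rest on assumed event rates, a two-sided 0.05 level and, for the wider range, the plan's own 50% withdrawal assumption. The test is not invalid. The improvement is worth making because harm is a foreseen consequence of the intervention.

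**What to change.** In the Statistical analysis section, replace the sentence on adverse health effects with wording to this effect: the main analysis is the between-arm risk difference with a 95% confidence interval (score or Newcombe method) for adverse health effects overall, and for cardiovascular events and death. It includes all randomised patients, so that deaths are not dropped from the denominator. The chi-square p-value is descriptive, and p > 0.05 will not be read as absence of harm.

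The cost is a change of wording, using data already collected. The downside is a less favourable safety statement, because the intervals will be wide: about ±2.7 to 2.9 percentage points with 3% in both arms.
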